### Interventions

#### Transcranial Direct Current Stimulation

A direct current will be applied by a pair of spongelike surface electrodes soaked in saline (35 cm^2^) and supplied by a specially developed constant current stimulator with a maximum output of 10 mA. To stimulate the DLPFC, the anode electrode will be placed over F3 according to the international 10-20 system for EEG electrode placement. The cathode will be placed over the contralateral supraorbital area (Figure 2).

**Figure 2 figure2:**
[figure not shown]
Transcranial direct current stimulation device.

For simulated stimulation, the electrodes will be placed in the same position; however, the stimulator will turn off after 20 seconds as described above. Therefore, the individuals felt the initial itching sensation at first, but they received no current for the remainder of the stimulation period. This procedure will allow the individuals to be blinded to the conditions of stimulation. A total of 10 stimulation sessions will be held for 2 consecutive weeks, with an interval of 2 days between the weeks. The duration of each session is 20 minutes. The applied intensity will be 2.0 mA [11,12,14].

Possible adverse effects are a tingling sensation and redness at the electrode site after stimulation. Headaches and burns may rarely occur. Possible side effects will be evaluated on a daily basis using a previously prepared questionnaire.

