## Methods

### Study Design

This is a prospective, parallel, double-blind, randomized controlled, and 2-armed clinical trial. This study will be single center and carried out on the premises of Faculdade São Leopoldo Mandic/Campinas, São Paulo, Brazil.

After an initial evaluation carried out by a research collaborator (collaborator 1), the participant will carry out the research protocol with another collaborator (collaborator 2) according to the draw performed by this collaborator. At the end of the protocol, the participant will again undergo an evaluation that will be performed by collaborator 1. Only collaborator 2 will know if the participant performed active stimulation or placebo. Therefore, this procedure will allow blinding of the participant and collaborator 1 (evaluator) to the stimulation conditions (Figure 1).

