### Assessments

Once eligibility and consent have been approved and completed, volunteers will undergo the Stroop test (based on the study by Campanholo et al [17]). This test consists of two tasks, one for reading and the other for naming the color. In both, the stimuli are color names printed in incongruous colors. The word-reading task gives an indication of reading fluency and serves to establish a benchmark for performance effectiveness relative to the color-naming task. The fact that there is an incongruity between the word name and the ink color causes an interference effect in the color naming. This interference is the Stroop color effect. Tests inspired by the Stroop effect are widely used in neuropsychology to measure individuals’ executive control and concentration [17].

After performing the Stroop test, the participant will undergo an assessment of cerebral blood flow by means of a transcranial Doppler ultrasound examination of the middle cerebral artery. The protocol developed by Rogge et al [18] will be carried out. Color-coded transcranial Doppler ultrasound will be performed in combined color and power mode with an ultrasound system equipped with a 2.5 mHz multifrequency probe transducer. Transtemporal insonation will be performed through the temporal bone window using axial and axial insonation plans and coronal with the participant in the right dorsal decubitus position. No eco-enhancer contrast will be used. Peak systolic and end diastolic pressure velocities will be measured in pulsed wave mode. Flow velocity measurements will be performed without angle correction. The examiner was free to optimize the images by changing the pulse gain and repetition frequencies [18].

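### Evaluator blinding rests only on withholding the allocation, while possible redness at the forehead electrode and an unstated gap before the final assessment leave it open to compromise

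*Protocol article*

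**What the plan says.** **Blinding.** Under Study Design, collaborator 1 assesses the participant before and after the protocol, and collaborator 2 runs the protocol in between. The article concludes that this arrangement blinds both the participant and collaborator 1. For the evaluator, the stated basis is "Only collaborator 2 will know if the participant performed active stimulation or placebo".

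**Electrodes.** Under Transcranial Direct Current Stimulation, a pair of saline sponges of 35 cm² is used: "the anode electrode will be placed over F3 according to the international 10-20 system for EEG electrode placement" and "The cathode will be placed over the contralateral supraorbital area".

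**Sham.** "For simulated stimulation, the electrodes will be placed in the same position", but "the stimulator will turn off after 20 seconds as described above". A session lasts 20 minutes, and there are 10 sessions. The sham is justified by the itching felt at the start, and only as a means of blinding the participants.

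**Skin signs.** "Possible adverse effects are a tingling sensation and redness at the electrode site after stimulation".

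**Assessments.** The evaluation consists of the Stroop test and a transtemporal Doppler examination, of which the Assessments section says: "The examiner was free to optimize the images by changing the pulse gain and repetition frequencies". Study Design places the closing evaluation after the protocol ends. Table 1 (as far as the extracted layout can be read) puts it in a column after the intervention ticks. Neither gives an interval.

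**The concern.** Withholding the allocation stops collaborator 1 from being told the arm. It does not stop collaborator 1 from seeing something that suggests it. The protocol names a possible visible sign, puts one electrode where that sign would show, and has the evaluator face the participant and work at the temple.

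At stake are both outcome sets. The primary outcome is Stroop correctness and execution time, obtained in an assessment run by collaborator 1. The secondary outcomes are Doppler velocities, for which the examiner may adjust the image settings. The article also states in advance the direction in which each is expected to move. An evaluator who suspects the arm could shift either result towards the hypothesis without meaning to. Blinding the evaluator is the protection the plan claims against this.

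**Working it through.** The plan gives no figure for how well the blind holds, so there is none to reproduce. The check is a chain of conditions, each set against the text.

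1. **Is there a possible visible sign?** Yes. Redness at the electrode site is listed as possible after stimulation.

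2. **Would the evaluator see it?** For the cathode, yes. The supraorbital area is exposed forehead skin, and the transtemporal Doppler brings the examiner close to it. No passage mentions covering the electrode sites.

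3. **Could it differ between arms?** It could.
   - Active session: 20 min × 60 = 1200 s.
   - Sham current: 20 s.
   - Ratio: 20/1200 = 0.0167, or 1.7% of the session time.

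   If redness depends on how long current flows, the arms would differ. If it comes from contact or moisture, they need not, because the sponges and their positions are the same in both arms. The document does not say which applies and gives no rate for either arm.

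4. **Does the sham cover this sign?** The text does not claim so. Its rationale is the initial sensation, and the people it sets out to blind are the participants.

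5. **Would the sign still be there at the final evaluation?** Unknown. Neither the duration of redness nor the gap after the last session is given. The Introduction reports that working-memory effects in healthy people can last up to 30 minutes after a session. That would be a reason to test soon, and the protocol permits it. It equally permits testing on a later day.

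**Can the effect on guessing be sized?** With equal allocation, an evaluator who guesses active whenever the skin is red is correct with probability 0.5 × P(red | active) + 0.5 × (1 − P(red | sham)). If the two rates are equal at any value r, this is 0.5r + 0.5(1 − r) = 0.5, which is chance. Any figure above 50% needs an assumed difference in rates, and the document supplies none. The result is therefore left without a number.

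**The case against.** The strongest reply is that this is an operational omission in a condensed article. Covering electrode sites is the kind of detail a full protocol may hold, and the article does describe both a separate evaluator and a sham. Nothing in the mention of redness contradicts either. This stands in part: the document does not contradict itself. But the article does more than stay silent. It presents evaluator blinding as following from the separation of roles, and its own description of the electrodes, the possible skin effect and the closing evaluation shows that this reasoning is incomplete.

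Three stronger readings are tempting and are not supported.

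- **That the protocol expects redness from active stimulation.** It calls redness possible and attributes it to neither arm. Sham participants wear the same sponges, and under Neurofeedback both groups have an EEG sensor on the forehead. Redness would be an imperfect cue at best.
- **That the blind will be broken at the final assessment.** This needs redness to persist until then, and the document gives neither its duration nor the interval.
- **That side-effect data are biased because an unblinded operator records them.** The article mentions a daily questionnaire but does not say who completes it or who sees it.

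**Conclusion.** The concern holds as a risk that the plan leaves open, not as a demonstrated failure. Evaluator blinding is claimed from withheld allocation alone, while a possible visible sign at an exposed electrode site is neither concealed nor separated in time from the final assessment.

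The risk matters only if two things are true: redness is more frequent or more marked after 20 minutes of current than after 20 seconds, and it is still visible when collaborator 1 makes the final assessment. The first is plausible from the 1.7% exposure ratio but is not stated. The second turns on the missing interval: it is a real possibility if assessment follows the last session directly, and perhaps a minor one on a later day. No size of bias can be derived. The case for acting is that the safeguard costs almost nothing and protects a property the trial claims to have.

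**What to change.** Two additions to the protocol:

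1. At the final evaluation, collaborator 2 places an identical headband or cap over the forehead and the F3 site of every participant, in both arms, before collaborator 1 enters. The temporal window stays free for the Doppler probe.
2. The protocol states the interval between the last stimulation session and the final Stroop and Doppler evaluation, the same for both arms.

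The cost is a headband or cap and two sentences of text. No extra staff, visit or procedure is needed, and stimulation is unchanged. The one drawback is slight inconvenience during the Doppler examination.

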#### Neurofeedback

In this study, we will use TuSion software to design the gaming environment and an EEG device and its Neurosky driver software. TuSion is free software designed to help improve cognitive skills while playing (Figure 3). The game design scheme was developed considering the following points: used hardware must be cheap and easy to handle, it should be simple to get a novice to get used to it in a short amount of time, and it should use neurofeedback to give a visual representation of attention levels and thus help improve it in a more attractive way. The ThinkGear software provided with the EEG device is used to connect the EEG device to the computer. It allows special apps and games to run according to the mental states detected by the EEG earplug with NeuroSky’s ThinkGear sensor. It is provided as an executable for Mac OS X and Windows platforms. Hardware includes a laptop or smartphone and a Neurosky “Mindwave Mobile” EEG device. The hardware for acquiring brain waves consists of a sensor that touches the forehead to collect data centered on the frontal cortex, the contact, and the reference points located in the earlobe. Data is processed using the integrated chip included in it. Both the eSense Meter (meditation and attention) and raw brain waves are calculated on the ThinkGear chip. The EEG electrode is placed on the user’s forehead (on the frontal cortex) during gameplay. The earplug safely measures and produces EEG power spectra (alpha waves, beta waves, etc), attention, meditation, and blink values. Attention and meditation are indicated and reported on a meter with a relative eSense scale from 1 to 100. This scale has a set of grouping schemes for the ranges of values, and a certain mental state is assigned to it. Values between 20-40 are reduced levels and 1-20 are considered a heavily reduced eSense. A value in the range of 40 to 60 is considered neutral. Values above 60 are considered values above normal or “high.” Values in the range of 80-100 are considered high eSense levels. Attention as an unsigned 1-byte value indicates the intensity of the user’s level of mental “focus” or “attention,” as occurs during intense concentration and directed (but steady) mental activity. Its value ranges from 0 to 100 (Figure 1). Distractions, wandering thoughts, lack of focus, or anxiety decrease attention meter levels [19,20].

**Figure 3 figure3:**
[figure not shown]
Electroencephalography device and its Neurosky driver software.

### Statistical Analysis

For the sociodemographic and epidemiological description of the groups, we will use the usual procedures of descriptive statistics such as calculation of frequencies and measures of central tendency and dispersion. The Shapiro-Wilk test will be performed to assess the assumption of normality of the outcome variables.

For analysis of paired and independent samples using a *t* test for comparisons within and between intervention groups or applying equivalent nonparametric tests (according to the results of the Shapiro-Wilk test) before and after the intervention, *P* values <.05 will be considered significant. Data will be organized and tabulated using SPSS (IBM Corp).

### Study Schedule

The schedule for the study is shown in Table 1.

**Table 1 table1:** The schedule of enrollment, interventions, and assessments.

			Study period												
			Enrollment		Allocation		Postallocation								Close-out
			–*t*_1_		0		*t* _1_		*t* _2_	*t* _3_		*t* _4_		*t* _ *x* _	
**Enrollment**															
	Eligibility screen	✓^a^													
	Informed consent	✓													
	Allocation			✓											
**Interventions**															
	Intervention A					✓		✓		✓	✓				
	Intervention B					✓		✓		✓	✓				
**Assessments**															
	Stroop test/US Doppler	✓		✓									✓		
	TDCS^b^ + neurofeedback							✓		✓	✓				

^a^Included at this time point.

^b^TDCS: transcranial direct current stimulation.

### Outcome Variables

The guiding theme of this study is to use tools or strategies to improve learning and promote better retention. The primary expected result is a greater correctness of answers in two phases of the Stroop test (word reading and color recognition) and a decrease in test execution time.

Secondary variables are based on physiological responses of cerebral blood flow where we expect to find an increase in velocity and systolic and diastolic peaks. This hypothesis is based on functional magnetic resonance studies where the results show an increase in local blood flow after the use of TDCS.

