**Objective:**

The aim of this study is to evaluate the effects of transcranial direct current stimulation associated with neurofeedback on declarative memory and cerebral blood flow in university students.

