Some studies covering healthy individuals support the hypothesis that TDCS improves performance involving working memories, compared to simulated stimulation (placebo), and these effects can last up to 30 minutes after the end of the session. Nitsche et al [15] proposed general exclusion criteria for TDCS in healthy individuals: individuals must be free from unstable medical conditions or any disease that may increase the risk of stimulation, for example, neurological diseases such as epilepsy or acute eczema under the electrodes. Additionally, they must not have metallic implants near the electrodes. Side effects such as itchiness, a burning sensation, or a headache are common but usually mild and with no long-term impact. Thus, TDCS compares favorably with other therapeutic approaches such as antidepressants or transcranial magnetic stimulation [15].

Noninvasive neuromodulation has emerged as an alternative to replace other forms of treatment such as pharmacological treatments, which although effective, have a high rate of side or adverse effects. Among the different types, neurofeedback and TDCS have shown to be promising approaches that can modify brain wave oscillation and can be used in the development of skills for the self-regulation of brain activity [16]. However, no data were found in the literature associating these two features. The aim of this trial is to investigate the effectiveness of TDCS on the dorsolateral prefrontal cortex (DLPFC) associated with neurofeedback evaluating behavioral and physiological parameters of healthy college students. We hypothesize that there will be a significant increase in declarative memory responses and increased cerebral blood flow using the proposed protocol.

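### The declarative-memory half of the objective and hypothesis is not measured by any listed outcome; the primary outcome, the Stroop test, measures something else by the protocol's own account

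*Protocol article*

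**What the plan says.** The Abstract of the protocol article gives the aim as to "evaluate the effects of transcranial direct current stimulation associated with neurofeedback on declarative memory and cerebral blood flow in university students". The Introduction ends with the matching hypothesis: "We hypothesize that there will be a significant increase in declarative memory responses and increased cerebral blood flow using the proposed protocol". The title carries the same term, and the Discussion again expects gains in declarative memory.

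The primary outcome, under Outcome Variables, is worded differently: "The primary expected result is a greater correctness of answers in two phases of the Stroop test (word reading and color recognition"), plus a reduction in the time taken to complete the test. The same section continues: "Secondary variables are based on physiological responses of cerebral blood flow".

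The Assessments section explains what the behavioural test captures: "Tests inspired by the Stroop effect are widely used in neuropsychology to measure individuals’ executive control and concentration". Of one of its two phases it says: "The word-reading task gives an indication of reading fluency and serves to establish a benchmark for performance effectiveness relative to the color-naming task". In the schedule (Table 1), the only efficacy row under assessments is "Stroop test/US Doppler"; the other row there lists the interventions themselves.

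**The concern.** A primary outcome should measure the construct that the objective and hypothesis name. Here the hypothesis concerns declarative memory, while the outcome is a speeded reading and colour-naming test that the protocol itself assigns to another cognitive domain.

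The interpretation of the primary result is at stake. A faster or more accurate Stroop performance, set beside the stated hypothesis, invites the conclusion that memory improved. A null Stroop result invites the conclusion that there is no memory effect. Neither conclusion would follow from the data collected.

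**Working it through.** No arithmetic decides this point. The check compares what the protocol article says it will learn with what it says it will measure.

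1. **Construct named.** The title, Objective, Introduction and Discussion all give declarative memory. The objective and hypothesis pair it with cerebral blood flow, so the objective has two parts.

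2. **What memory means in this document.** The Discussion describes memory as storing learned material and calling it up later. The prior work it cites for memory effects of prefrontal stimulation used word memorization tasks with later recognition.

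3. **What is measured.** Assessments, Table 1 and Outcome Variables agree on two efficacy assessments:

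| Assessment | Role | What the protocol says it reflects | Part of the objective covered |
|---|---|---|---|
| Stroop, word reading | Primary | Reading fluency; a benchmark for colour naming | None |
| Stroop, colour naming | Primary | Interference; executive control and concentration | None |
| Transcranial Doppler, middle cerebral artery | Secondary | Flow velocities | Cerebral blood flow |

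4. **Is a memory task hidden in the Stroop test?** As described under Assessments, the participant reads colour words or names the ink they are printed in. Nothing is learned and then recalled or recognised.

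5. **Is a proxy argument made?** None appears in Assessments, Outcome Variables or the Discussion.

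6. **Could another recorded variable serve?** The EEG device produces attention and meditation values (Neurofeedback section). They belong to the intervention, are not listed as outcomes, and are not memory measures.

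7. **Would the sample size carry over to a memory endpoint?** The Sample section gives 25 per group for a 40% difference in proportions, alpha .05 and power 0.80, without a control proportion. Reading this as 40 percentage points, two-sided, the standard two-proportion formula without continuity correction gives 23 to 24 per group for assumed control proportions of 0.20 to 0.40. With continuity correction it gives 25 at 0.10 versus 0.50. The stated figure is thus reproducible under an assumed control proportion, but it is not tied to a memory measure. The document gives no effect size or SD from which a size for one could be computed.

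Result: of the two parts of the objective, one (blood flow) has an outcome and one (declarative memory) has none. The unmeasured part is the one the behavioural primary outcome would be expected to serve.

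**The case against.** Several defences deserve an answer.

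- **A journal article condenses the full protocol.** True, but the primary outcome is expressly named, and three places list the same assessments. This is a stated mismatch, not a detail left to another document.
- **Attention and executive control support memory.** The protocol does not make that argument. Even if it did, a change in attention would not by itself show a change in declarative memory.
- **The Introduction also frames the aim more broadly, as behavioural and physiological parameters.** It does, but the next sentence gives the hypothesis in terms of declarative memory.
- **The trial still answers part of its question.** This stands. A reader might infer that the trial cannot answer its stated question at all. The documents do not support that, because Doppler addresses blood flow as a declared secondary outcome.
- **No rule says that a Stroop gain will be reported as a memory gain.** This also stands. Outcome Variables words the expected result in Stroop terms, and the Abstract's conclusion promises only preliminary results on the benefits of the two tools. The misreading is a strong risk, given the title, objective, hypothesis and Discussion, but it is an inference about how the result will be read.

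**Conclusion.** The mismatch is real and affects the interpretation of the primary result. The declarative-memory part of the objective and hypothesis has no outcome; the blood-flow part has one. Read against the hypothesis as written, either a positive or a null Stroop result could be mistaken for evidence about declarative memory.

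A reader might also infer that relabelling the whole Stroop outcome as executive control would settle the matter. It would not. The primary outcome includes the word-reading phase, which the Assessments section treats as a reading-fluency benchmark, so a gain there would still carry the wrong label.

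The conclusion rests on the protocol's own account of what the Stroop test measures and on its list of assessments being complete for efficacy. It needs no outside view of the test.

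**What to change.** Restate the objective, hypothesis and planned conclusion, and the title in later reports, as the effect on executive control and concentration measured by Stroop colour naming. Report word reading separately as the reading-fluency benchmark. Keep blood flow as it is, and draw no declarative-memory conclusion from this trial.

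The Results section says that enrolment began in July 2022 and that analysis of the secondary outcomes is in progress. The restatement is therefore a change to a running trial: date it and disclose it before the primary results are interpreted. The registry entry is not shown, so check whether it needs the same change.

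This adds no participants or procedures. The price is a narrower claim than the title suggests.

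Keeping the declarative-memory claim would need an added recall or recognition measure with its own sample size basis. That is not a cheap change once enrolment has started. Its timing would also need settling: Table 1, as extracted, ticks the Stroop and Doppler assessment in three columns, whereas Study Design describes one evaluation before and one after the intervention.

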### Sample

The sample of 50 volunteers was calculated assuming a 40% difference in the proportion between the active TDCS and placebo groups in performance before and after the interventions. This calculation was performed using an online statistical program, considering an alpha of .05 and a power of 0.80, resulting in a sample of 25 individuals in each group (intervention and control). To approximate unexpected factors, we applied a 20% dropout rate, reaching a total sample size of 60 individuals.

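### The primary Stroop outcome is two to four measures, each judged at P<.05 with no lead measure and no success rule, so the primary claim lacks either the 5% error rate or the planned 0.80 power

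*Protocol article*

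**What the plan says.** Three sections of the protocol article bear on this.

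- **Outcome Variables** gives the primary expected result as "greater correctness of answers in two phases of the Stroop test (word reading and color recognition) and a decrease in test execution time". The Assessments section confirms that the two phases are separate tasks: "This test consists of two tasks, one for reading and the other for naming the color".
- **Statistical Analysis** plans t tests "for comparisons within and between intervention groups or applying equivalent nonparametric tests" and sets a single criterion for all of them: P "values <.05 will be considered significant".
- **Sample** makes one calculation, "assuming a 40% difference in the proportion between the active TDCS and placebo groups in performance before and after the interventions", "considering an alpha of .05 and a power of 0.80". It arrives at 25 per group.

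The article names no single primary variable and no combined score. It does not say how a mixed result, with some measures significant and others not, would be read.

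**The concern.** The primary outcome contains several quantities. One correctness score over both phases plus one total time gives two. Correctness per phase plus one total time gives three. Correctness and time per phase gives four. Each is tested at .05, so whether the trial has succeeded depends on a rule that the protocol does not state.

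If one significant measure is enough, the error rate for the primary claim exceeds the nominal level. If all are required, the 0.80 power planned for one comparison does not carry over to the claim. With the rule left open, the choice between the two can be made after the results are seen, and no later analysis can undo that.

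Mixed results are plausible. A participant who answers faster at the cost of more errors improves on one primary measure and worsens on another. That trade-off is reasoning about the test, not something the article states. The point needs only that no rule exists for reading such a result.

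**Working it through.** **Inputs from the article.** Alpha .05, power 0.80, 25 per group, a 40% difference in a proportion (Sample); P<.05 for every test (Statistical Analysis); the primary components (Outcome Variables).

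**Assumptions, because the article is silent.** Two-sided tests; k = 2, 3 or 4 measures; equal correlation between measures of 0 to 0.9; 80% power for each measure alone.

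**1. The plan's own figure.** The usual two-proportion formula is

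n = [z(.975)·√(2p̄(1−p̄)) + z(.80)·√(p1(1−p1)+p2(1−p2))]² / (p2−p1)².

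No base rate is given. For 30% against 70%:

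(1.960×0.7071 + 0.8416×0.6481)² / 0.16 = 23.3, so 24 per group.

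With continuity correction, 10% against 50% gives exactly 25. The stated 25 is therefore reproduced, for a single comparison. It contains no allowance for several primary measures. It also does not identify which measure is meant: execution time is not a proportion, while either correctness score could be one.

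**2. Any one measure suffices, no true effect.** With uncorrelated measures:

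- P<.05 in either direction: 1 − .95^k = 9.8%, 14.3%, 18.5% for k = 2, 3, 4.
- P<.05 in the favourable direction only: 1 − .975^k = 4.9%, 7.3%, 9.6%, against 2.5% for one test.

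**3. All measures must succeed, each with 80% power.** With uncorrelated measures: .8^k = 64%, 51%, 41%.

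**4. Correlated measures.** These figures come from 1,000,000 simulated sets of equally correlated normal test statistics. The zero-correlation rows are the exact values above.

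| Measures | Correlation | Any, either direction | Any, favourable only | All succeed (power) |
|---|---|---|---|---|
| 2 | 0 | 9.8% | 4.9% | 64% |
| 2 | 0.5 | 9.0% | 4.5% | 69% |
| 2 | 0.9 | 7.0% | 3.5% | 75% |
| 3 | 0 | 14.3% | 7.3% | 51% |
| 3 | 0.5 | 12.6% | 6.3% | 61% |
| 3 | 0.7 | 10.9% | 5.5% | 66% |
| 3 | 0.9 | 8.4% | 4.2% | 72% |
| 4 | 0 | 18.5% | 9.6% | 41% |
| 4 | 0.5 | 15.6% | 7.8% | 56% |
| 4 | 0.7 | 13.0% | 6.5% | 62% |
| 4 | 0.9 | 9.3% | 4.7% | 70% |

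A separate simulation of 20,000 trials with t tests at 25 per arm, for three and four measures, agrees within about half a percentage point for the either-direction rates and for the power.

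Only between-arm tests are counted. The within-group tests planned at the same threshold would add further chances of a false positive.

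**The case against.** **The error rate may be read too strongly.** A reader might infer that the trial carries a 12-19% risk of falsely declaring stimulation effective. The documents do not support that. That range counts significance in either direction, whereas the stated hypothesis is directional. It also assumes three or four measures and correlations no higher than about 0.5, and the article gives no correlation. For a false claim of benefit with two-sided tests, the range is about 3.5-10% against 2.5%. The relative inflation is similar, but the absolute figure is about half as large.

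**The number of measures is not settled.** The wording can be read as one correctness score and one time, and the scoring follows a cited source that is not shown. This stands, which is why two measures are included.

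**The conjunction may mean that all must improve.** The article speaks of one primary expected result and joins its parts with *and*. On that reading no error inflation arises. This also stands. The problem then moves to power, which is below 0.80 in every case computed. The size of that shortfall depends on the assumed 80% per measure.

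**Multiplicity is commonly left to an analysis plan, and this is a condensed article reporting preliminary work.** The choice of adjustment method could indeed be left there. Defining the primary outcome cannot. The article lists several measures as primary and fixes a flat P<.05, so a plan that picked one measure would be changing the stated outcome, not filling in a detail. A preliminary study still needs to know what its primary result is.

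**Conclusion.** The point holds. The primary claim rests on two to four Stroop measures, each judged at P<.05, with no lead measure and no success rule.

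- **Any measure suffices:** the chance of at least one between-arm P<.05 under the null, in either direction, is about 7-10% (two), 9-14% (three) or 9-19% (four). Counting only favourable results, it is about 3.5-10% against 2.5%.
- **All must succeed:** alpha is protected, and joint power is about 64-75% (two), 51-72% (three) or 41-70% (four).

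The ranges run over assumed correlations between 0 and 0.9 and assume two-sided tests. The power figures also assume 80% for each measure. The Sample section does not establish that, since it sizes an unspecified proportion while the analysis uses t tests. The exact sizes are therefore uncertain. The conclusion that neither reading delivers both the nominal error rate and the stated power holds across the whole range.

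**What to change.** Before any outcome data are examined by arm, name one primary Stroop measure in Outcome Variables, compared between arms at two-sided .05, and list the other correctness and time measures as secondary. Which measure to name is the sponsor's choice. A score combining speed and correctness is possible but is not required by this point.

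If several measures stay primary, state one of these rules in Statistical Analysis and Outcome Variables, and restate the power in Sample for the chosen rule:

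- **Any measure suffices:** Holm's procedure at an overall .05.
- **All must reach .05:** no division of alpha is needed.

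**Cost.** Naming one measure is a wording change that needs no new data; its downside is that some measures become secondary. Under either alternative the stated power becomes less favourable. With three measures, each with 80% power at .05, one measure's power at Holm's strictest step (.05/3 = .0167) is about 65%. The chance of at least one rejection is about 82-96% for correlations from 0.7 down to 0, if all three effects are real. Keeping 80% power for a single measure at an evenly divided alpha, for 30% against 70%, would raise the size from 24 per group to 32 (three measures) or 34 (four), before dropout. For the all-must-succeed rule, the last column of the table shows the power to be made up.
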